## Collaborative Arrangements

Describe briefly if this study involves any scientific, administrative, fiscal, or programmatic arrangements with other national or international organizations or individuals. Indicate the nature and extent of collaboration and include a letter of agreement between the applicant or his/her organization and the collaborating organization.

None. We will work with MOHFW or City Corporation officials in the participating sites.

#

# Budget Justifications

­­

Please provide one page statement justifying the budgeted amount for each major item. Justify use of human resources, major equipment, and laboratory services.

**Personnel:**

PI: 20% time, already covered under SUZY grant

Data manager/statistician: (NOA 50%) Responsible for data quality, management and statistical analyses

Field Coordinator: (NOA FT) Responsible for implementation and conduct of surveys in all sites. This includes preparing field sites for visits.

FROs: They will supervise a team of 8 FRAs each.

FRAs: They will carry out the interviews/data collection. The # of FRAs is based upon the anticipated average # of completed interviews per week and the need to complte on survey round in 10 weeks.

Travel:

Vans, with a driver, will be rented locally if required. We will need two 12 seaters (with the exception of the Dhaka sites).

Per-diems are based upon Centre rates and an estimated 90 days in the field.

The investigators will visit the field sites on six occasions.

Rental:

To support the field sites $5,000 has been budgeted for Kamalapur, Mirsarai, Abhoynagar, Mirpur and Sylhet.

Equipment:

One desktop PC and printer will be purchased for use by the data management unit.

#

# Other Support

Describe sources, amount, duration, and grant number of all other research funding currently granted to PI or under consideration.

none for this proposed study

**Appendix 2: Comments of External Reviewers**

## Appendix 3: Response to External Reviewer’s Comments

The comments and response to the external review carried out at the time of the initial RRC submission are attached.

## Appendix 4: Abstract Summary covering eight points specified by the ERC

**INFORMATION TO INCLUDE IN ABSTRACT SUMMARY**

The Committee will not consider any application which does not include an abstract summary. The abstract should summarize the purpose of the study, the methods and procedures to be used, by addressing each of the following items. If an item is not applicable, please note accordingly:

1. Describe the requirements for a subject population and explain the rationale for using in this population special groups such as children, or groups whose ability to give voluntary informed consent may be in question.

***This survey will focus on under –five diarrheal illness episodes, as this is the recommended age-group to receive zinc treatment. Informed, voluntary consent will be obtained from the parent or primary guardian.***

1. Describe and assess any potential risks – physical, psychological, social, legal or other – and assess the likelihood and seriousness of such risks. If methods of research create potential risks, describe other methods, if any, that were considered and why they will not be used.

***There are no risks we can identify that are associated with this survey*.**

1. Describe procedures for protecting against or minimizing potential risks and an assessment of their likely effectiveness.

# *None*

1. Include a description of the methods for safeguarding confidentiality or protecting anonymity.

***There is no identifying information onn the questionnaire. All questionnaires will be placed in a locked cabinet or box at the end of each day.***

1. When there are potential risks to the subject, or the privacy of the individual may be involved, the investigator is required to obtain a signed informed consent statement from the subject. For minors, informed consent must be obtained from the authorized legal guardian or parents of the subject. Describe consent procedures to be followed including how and where informed consent will be obtained.
2. If signed consent will not be obtained, explain why this requirement should be waived and provide an alternative procedure.

***We will obtain a verbal consent and require the interviewer to sign off that this was obtained. The questions to be asked are not threatening nor does this information place anyone at risk for physical, psychological or social harm.***

1. If information is to be withheld from a subject, justify this course of action.

***No information is being withheld****.*

1. If there is a potential risk to the subject or privacy of the individual is involved in any particular procedure include a statement in the consent form stating whether or not compensation and/or treatment will be available.

***No potential risks have been identified.***

1. If study involves an interview, describe where and in what context the interview will take place. State approximate length of time required for the interview.

***The interview will take place in the child’s home at a time convenient for the parent/guardian. It requires approximately 20 minutes to complete.***

1. Assess the potential benefits to be gained by the individual subject as well as the benefits which may accrue to society in general as a result of the planned work. Indicate how the benefits outweigh the risks.

***Following the interview, all unaware participants will be informed of the usefulness of zinc. From a societal standpoint, the findings of this survey guide the equitable scale up of zinc across Bangladesh.***

1. State if the activity requires the use of records (hospital, medical, birth, death or other), organs, tissues, body fluids, the fetus or the abortus.

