## Hypothesis to be Tested:

Concisely list in order, the hypothesis to be tested and the Specific Aims of the proposed study. Provide the scientific basis of the hypothesis, critically examining the observations leading to the formulation of the hypothesis.

Over the planned 8 months of observation;

H1: That there will be a significant, upward trend in use of zinc for the treatment of childhood diarrhea.

H2: That there will be a significant downward trend in the use of antibiotics for the treatment of non-bloody childhood diarrhea

H3: That there will be disparities in zinc treatment coverage on the basis of household income status. gender oand location (rural, urban, city corporation slum and non-slum populations).

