## Research Design and Methods

Describe in detail the methods and procedures that will be used to accomplish the objectives and specific aims of the project. Discuss the alternative methods that are available and justify the use of the method proposed in the study. Justify the scientific validity of the methodological approach (biomedical, social, or environmental) as an investigation tool to achieve the specific aims. Discuss the limitations and difficulties of the proposed procedures and sufficiently justify the use of them. Discuss the ethical issues related to biomedical and social research for employing special procedures, such as invasive procedures in sick children, use of isotopes or any other hazardous materials, or social questionnaires relating to individual privacy. Point out safety procedures to be observed for protection of individuals during any situations or materials that may be injurious to human health. The methodology section should be sufficiently descriptive to allow the reviewers to make valid and unambiguous assessment of the project.

Study design: A repeat, ecologic survey in three rural upazillas, three municipalities and two city coprporation slum plus two non-slum zones is proposed. The survey team will complete three survey cycles per site, each cycle estimated to require 10 weeks to complete. The surveys will be carried out from September, 2006 through April, 2007 (SUZY Project funding ends in June, 2007).

Survey Populations

a. Rural: The sub-districts of Mirsarai, Abhoynagar and Hobiganj have been purposively selected. Within

each sub-district we will randomly select 20 clusters based upon a listing of all wards in the subdistrict.

All wards will be enumerated and then randomly selected.

b. Urban: The district municipalities of Khulna, Camila and Sylhet have been purposively selected. Twenty

clusters will be randomly selected within each municipality. Clusters are defined as geographic units

(“strata”) within the municipality that will be enumerated.

c. Dhaka City Corporation: slum zones of Kamalapur and Mirpur, non-slum zones (and wards) of Green

Road and Old Dhaka. Within each zone 20 clusters will be selected. Clusters are geographically defined

population“units” based upon the most recent census

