Within each cluster a household census survey will be completed for the identification of any under -five child who has had a diarrheal ilness in the past two weeks of at least 2 days duration. The aim is to identify 16 cases per cluster.

Within each site, random cluster selection will be repeated at the time of each new survey round. The sampling framework is summarized in figure 1.

CHILDREN UNDER FIVE YEARS OF AGE

Diarrheal Disease Episode in past 2 weeks and

at least 48 hrs duration

Dhaka Urban Municipalities Rural Upazillas

2 slum zones Khulna Abhoynagar

2 non-slum zones Camila Mirsarai

Sylhet Hobiganj

random random random

20 clusters 20 clusters 20 clusters

per zone per municipality per upazilla

at 16 casesper cluster

n=320 cases per site

N= 640 slum N=960 N=960

N= 640 non-slum urban municipal rural cases

per round per round per round

Figure 1. Summary of sampling frame for cluster surveys

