## Sample Size Calculation and Outcome Variable(s)

For each survey round (weeks 1 to10, 12 to 21 , 23 to 32 weeks) we are determining estimates of zinc, ORS and antibiotic use (prevalence). With each new interval we will be sampling from the same sites, but will carry out a new random selection of clusters in which cases will be identified.

As depicted in figure 1, for each survey round the number of subjects by site and location is as follows:

Location Sites N/site N/location

City corporations Slums x 2 320 640

Non-slums x 2 320 640

Urban Municipalities x 3 320 960

Rural Upazillas x 3 320 960

Based upon WHO EPI cluster survey methods, the design effect is estimated to be 2.0 (11)

a. Prevalence of zinc treatment by site: Setting confidence at 0.95 and a minimal detectable error of a 5% for a prevalence estimate within a site, assuming the baseline overall prevalence of zinc coverage to be 10%:

(Z alpha )2 (P)(1-P)

N/site = x 2 (cluster adjustment design effect)

d 2

N/site = 276 cases

b. Trends in use of ORS and antibiotics by site: Setting confidence at 0.95 and a minimal detectable error of 10% around a prevalence of 50% of cases being treated with ORS or an antibiotic;

N/site = 198

d. Comparison of two proportions (hypothesis testing):

To examine whether zinc coverage in urban or rural locations is significantly different among males vs females, setting the level of conficence at .95 (one-sided), power at .80, minimal detectable difference 10%, assuming an overall prevalence of 25% coverage by the third cycle

(Z alpha + Z beta)2 (P)(P-1) x 2

N/gender/location = x 2 (cluster adjustment design effect)

d 2

N/location = 461

Given these estimates, we will have the power to detect smaller differences in the rural and municipality

locations. In the City Corporations sites the power is adequate if we combine slum and non-slum populations. Keeping them separate will allow for a minimal detectable difference of 12%.

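### Interviewers tell unaware caretakers about zinc, and later rounds do not exclude clusters already visited, so the between-round rise may overstate the impact of the roll-out

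*Protocol*

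**What the plan says.** In the protocol's Appendix 4 (Abstract Summary), the item on benefits commits the field team to a short piece of health education: "Following the interview, all unaware participants will be informed of the usefulness of zinc". It applies in every round, and the listeners are caretakers of under-fives who have just had diarrhoea.

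Research Design and Methods sets the repetition: "The survey team will complete three survey cycles per site, each cycle estimated to require 10 weeks to complete". The ten sites are fixed and purposively chosen. In the rural sites, "we will randomly select 20 clusters based upon a listing of all wards in the subdistrict", and 20 clusters are also taken in each municipality and each city zone. Within a cluster, "The aim is to identify 16 cases per cluster". For later rounds, "Within each site, random cluster selection will be repeated at the time of each new survey round". The sample size section repeats the rule: "With each new interval we will be sampling from the same sites, but will carry out a new random selection of clusters".

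H1 reads: "That there will be a significant, upward trend in use of zinc for the treatment of childhood diarrhea". The Background section makes round 1 the reference point, taken after providers had been briefed and before the advertising starts. The protocol's title speaks of monitoring impact.

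**The concern.** The survey delivers a small dose of the message whose uptake it measures. Talking about zinc after the interview protects that interview, but not a later round that returns to the same place. Round 1 cannot be affected. Rounds 2 and 3 can, and the expected direction is upward, towards the predicted trend.

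There is no concurrent comparison area, so nothing in the design nets this effect out. At stake is how the rise is interpreted: part of what is credited to the roll-out could come from the interviewers' own visits.

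**Working it through.** The plan gives no figure for overlap or contamination, so there is none to reproduce on this point. Its sampling counts are consistent: 20 clusters × 16 cases = 320 per site, and 640 + 640 + 960 + 960 = 3,200 per round.

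**Inputs from the protocol.** 20 clusters per site per round; 16 cases per cluster; three rounds; the same sites; zinc coverage assumed at 10% at baseline and 25% by the third cycle (a 15-point rise); design effect 2.0.

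**Inputs assumed, because the protocol does not give them.** Clusters per site, M; the share f of a cluster's under-fives interviewed in one round, 5 to 10% (16 cases would mean 320 to 160 under-fives per cluster); the excess in zinc use among informed households, u, 20 to 50 points. Each draw is taken as independent, with every cluster eligible.

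**Step 1: clusters visited before.** The round-2 share is 20/M. The round-3 share is 1 − (1 − 20/M)².

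| M | Round 2 | Round 3 |
|---|---|---|
| 40 | 50% | 75% |
| 60 | 33% | 56% |
| 100 | 20% | 36% |
| 200 | 10% | 19% |

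The chance that round 2 re-uses no cluster in a given site is 0.7% at M = 100 and 11% at M = 200. Below M = 40 some overlap is certain.

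**Step 2: round-3 cases from an informed household.** With no spread to neighbours and no excess recurrence, the share is 1 − (1 − 20f/M)². At M = 100:

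- f = 0.05: 1 − 0.99² = 2.0%
- f = 0.10: 1 − 0.98² = 4.0%

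**Step 3: inflation of the round-3 estimate** (informed share × u).

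- M = 100: 0.0199 × 20 = 0.4 points, up to 0.0396 × 50 = 2.0 points
- M = 200: (1 − 0.995²) × 20 = 0.2 points, up to (1 − 0.99²) × 50 = 1.0 point
- M = 40: (1 − 0.975²) × 20 = 1.0 point, up to (1 − 0.95²) × 50 = 4.9 points

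**Step 4: sensitivity to recurrence.** If an interviewed child were three times as likely to be a case again, 20f/M becomes 60f/M. At M = 100 the range becomes (1 − 0.97²) × 20 = 1.2 points to (1 − 0.94²) × 50 = 5.8 points.

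**Step 5: effect on a test of round 3 against round 1.** Suppose coverage truly stayed at 10%. The standard error of the difference is √(2 × 2.0 × 0.10 × 0.90 / n): 1.94 points at n = 960 per round and 1.06 points at n = 3,200. The two-sided 5% error then becomes:

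| Bias | n = 960 | n = 3,200 |
|---|---|---|
| 1 point | 8% | 16% |
| 2 points | 18% | 47% |

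**The case against.** Four points can be made on the other side.

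- **H1 does not attribute.** A reader might infer that H1 credits the rise to the campaign. It claims only an upward trend, and the Project Summary and Specific Aims describe changes that coincide with the roll-out. Zinc given because an interviewer mentioned it is still real use, and a fresh random draw from all clusters still estimates actual coverage in that round. This stands: the concern is about reading the trend as impact, not about an error in the trend estimate.
- **Re-use is traceable.** A reader might infer that contamination could never be separated afterwards. At cluster level that is not so. Clusters come from enumerated lists, and the survey analysis named under Data Analysis needs a cluster identifier for each case. Only repeat households are lost, because Appendix 4 says questionnaires carry no identifying information.
- **Re-interview is not shown.** The protocol is silent on whether earlier clusters stay eligible. Cluster overlap is likely under independent draws, but that particular households will be seen twice does not follow.
- **Larger sizes are not supported.** One could apply an assumed 2 to 10 point effect to every case in a revisited cluster and obtain 0.4 points (19% × 2, M = 200) to 5.6 points (56% × 10, M = 60). But only about 16 caretakers per cluster are interviewed, and only the unaware are told. The Background section also says provider awareness is already high, which may shrink the unaware group. Spread to neighbours would work the other way, but the documents give no basis for its size.

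What remains is that nothing prevents re-selection, and that any resulting bias runs towards the expected finding.

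**Conclusion.** The concern holds in a limited form. The protocol lets the survey's own zinc message reach clusters that later rounds may sample, and this can inflate the between-round rise when it is taken as the impact of the roll-out.

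The size cannot be fixed from the documents. About 0.4 to 2 points at 100 clusters per site rests on the assumed M, f and u, on independent draws, on every interviewed household being newly informed, and on no neighbour spread or excess recurrence. Against a 15-point rise that is second-order. It would matter if the true rise were small or a site had few clusters. H3's within-round comparisons are less exposed, and no sample-size figure is called into question. This is a worthwhile, inexpensive improvement rather than a defect that undermines the survey.

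**What to change.** In each site, draw 60 clusters once, without replacement, and allocate 20 at random to each round. Each round is still a random sample of the site's clusters, and re-selection is removed. Caretakers can still be informed as planned. The rule has to be in place before round 2 is drawn.

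Where a site has fewer than 60 clusters:

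- keep re-use to the minimum, and mark re-used clusters from the sampling list;
- add one yes/no item asking whether this survey has interviewed the household before, which needs no identifier;
- repeat the trend analysis without previously interviewed households, and also without re-used clusters where enough fresh clusters remain. This last step can fail: with 40 clusters and no overlap between rounds 1 and 2, round 3 has no fresh cluster left.

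The cost is one extra question and the loss of any variance gain from chance overlap of clusters between rounds.

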#### *None required*

The statement to the subject should include information specified in item 2,3,4,5(c) and 7 as well as indicating the approximate time required for participation in the activity.

Check-List

